## 2. Methods and Analysis

### 2.1. Trial Design

This is a parallel-design and randomized controlled trial. The subjects will be recruited from the Rehabilitation Center of the First Affiliated Hospital of the Henan University of Chinese Medicine. We selected 177 patients who meet the predefined criteria and randomly divided them into 3 groups, with 59 patients in each group: experimental group (GV-EA), control group 1 (conventional EA), and control group 2 (rehabilitation treatment). All patients will receive 20 sessions of treatment that last for 4 weeks and will have sEMG measurements before and after treatment. The efficacy of GV-EA relative to conventional EA and rehabilitation treatment will be analyzed after data collection. The study flow chart is shown in Figure 1. An example template for the content of admission plans, interventions, and evaluations is shown in Table 1. This protocol is guided by the Standard Protocol Items: Recommendations for Interventional Trials (SPIRIT) [17].

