#### 2.6.3. Acupuncture Interventions

In China, stroke patients are familiar with acupuncture treatment. Thus, it is easy for patients to determine whether fake acupuncture is used. And because an important purpose of this trial is to make up for the lack of comparison of the efficacy differences between different acupuncture acupoints in the current experiment, placebo acupuncture was not selected. Therefore, we decided to perform clinical conventional electroacupuncture as the control group rather than sham acupuncture and placebo acupuncture.

The interventions will be performed by acupuncturists with more than 3 years of experience in rich clinical acupuncture practice. The acupuncture treatment group used sterilized stainless steel disposable acupuncture needles (0.3∗30 mm). After the needle is inserted to a certain depth of points, it will be lifted and thrust or twirled and rotated for Deqi sensation. After feeling of “Deqi”(the sensations including soreness, numbness, distention, or heaviness), it was connected to the electroacupuncture device (G6805-2A, Shanghai Huayi Medical Instrument Co., Ltd., China, dense waves 2–5 times/second, frequency 2.5 Hz), once a day, every 30 minutes, 5 times a week, for 4 weeks.

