### 2.7. Sample Size

The purpose of this study is to evaluate the efficacy of GV-EA in the treatment of poststroke lower limb spasticity. Based on previous studies and clinical experience, the effectiveness rate of conventional EA and rehabilitation treatment is about 75% and 60%, and it is expected that electroacupuncture of GV acupoint will reach 90% [19]. Type 1 error is assumed at 0.05, type 2 error is assumed at 0.1, and a standard deviation is 10. PASS15.0 software (NCSS Statistical Software, Kaysville, UT, USA) has been used to determine the sample size, and the minimum sample size is 53 subjects for each group. Considering a dropout rate of 10%, a total of 177 subjects will be required with 1:1:1 allocation to each group (59 participants per group) for this study.

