### 4.4. Statistical Analysis

Statistical analysis will be performed using SPSS 25.0 software for statistical analysis. To measure baseline, a chi-square test or analysis of variance (ANOVA) is used to compare demographic data and other basic data at baseline. Continuous variables are expressed in terms of mean ± standard deviation when following a normal distribution. If not, the data will be shown by medians and interquartile ranges. Frequencies and percentages will be used to count the data. The paired *t*-test will be used to compare the differences between the groups before and after treatment, including the RMS value, FMA-LE, and MBI score. The comparison among the three groups before and after treatment will be analyzed by variance (ANOVA). For the MAS, the Kruskal–Wallis test will be used. The test level is set to 0.05, and *P* < 0.05 means the difference is statistically significant.

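### The stated type 2 error of 0.1 at 53 per group holds only for a three-group test of the assumed rates; GV-EA versus conventional EA has about 53% power

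*Protocol article*

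**What the plan says.** Section 2.7 (Sample Size) assumes that "the effectiveness rate of conventional EA and rehabilitation treatment is about 75% and 60" per cent respectively, and that "it is expected that electroacupuncture of GV acupoint will reach 90" per cent. It adds "Type 1 error is assumed at 0.05" and "type 2 error is assumed at 0.1", mentions a standard deviation of 10, and concludes that "the minimum sample size is 53 subjects for each group". A 10% dropout allowance raises this to 59 per group, 177 in total. The section names neither the test nor the comparison that was powered, and gives neither the sidedness of alpha nor any adjustment of it.

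Section 2.1 (Trial Design) states the question as two comparisons: "The efficacy of GV-EA relative to conventional EA and rehabilitation treatment will be analyzed after data collection". Section 2.6.3 defends conventional EA over a sham control on the ground that "an important purpose of this trial is to make up for the lack of comparison of the efficacy differences between different acupuncture acupoints".

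For the between-group analysis, section 4.4 (Statistical Analysis) says: "The comparison among the three groups before and after treatment will be analyzed by variance (ANOVA"). The MAS is to be analysed with the Kruskal–Wallis test.

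**The concern.** A reader of section 2.7 will take the type 2 error of 0.1 to cover the comparisons announced in section 2.1, including GV-EA against conventional EA, which section 2.6.3 singles out. Three rates spaced 15 points apart are much easier to tell from a common rate than two neighbouring rates are to tell from each other. A size chosen for the three-group test can therefore leave the neighbouring pair badly underpowered.

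Two misreadings are at stake. A non-significant GV-EA versus conventional EA result could be taken as evidence that the two acupoint sets work equally well, when the trial had little better than an even chance of detecting the assumed 15-point difference. A significant three-group result could be credited to GV-EA over conventional EA when the pairwise contrast does not show it.

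**Working it through.** **Inputs, all from section 2.7:** rates 0.90 (GV-EA), 0.75 (conventional EA) and 0.60 (rehabilitation); alpha 0.05; type 2 error 0.1; 53 per group; dropout 10%. Two-sided, unadjusted testing is my assumption, and variants are shown. The standard deviation of 10 does not enter a comparison of rates.

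**1. Reproducing 53: three-group chi-square, 2 df.**
- Mean rate = (0.90 + 0.75 + 0.60)/3 = 0.75.
- w² = [(0.15² + 0² + 0.15²)/3] / (0.75 × 0.25) = 0.015/0.1875 = 0.08.
- Noncentrality = N × w². At 53 per group, N = 159 and 159 × 0.08 = 12.72, giving power 90.2%. At 52 per group, 156 × 0.08 = 12.48, giving 89.6%.
- So 53 is the smallest size that reaches 90%. Simulating the test itself gives about 92.5%.
- Dropout: 53/0.90 = 58.9, rounded up to 59; 3 × 59 = 177.

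**2. Do other readings give 53?** For 90% power at two-sided 0.05, a test of two proportions needs 133 per group (90% vs 75%), 42 (90% vs 60%; 49 with continuity correction) or 203 (75% vs 60%). One-sided, these become 109, 34 and 166. Treating the rates as means with SD 10 needs about 5 per group by ANOVA, or 10 for two means 15 apart. The one near miss is 90% vs 60% at alpha 0.05/3, which gives 54 (pooled variance) or 52 (arcsine). Section 2.7 states no such adjustment, and that test would not cover conventional EA.

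**3. Pairwise power at 53 per arm.**

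Power = Φ{[d√n − z√(2p̄(1−p̄))] / √(p₁(1−p₁) + p₂(1−p₂))}, with z = 1.960.

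- *GV-EA vs conventional EA:* d = 0.15, p̄ = 0.825. √(2 × 0.825 × 0.175) = 0.5374; √(0.09 + 0.1875) = 0.5268. (0.15 × 7.280 − 1.960 × 0.5374)/0.5268 = (1.0920 − 1.0532)/0.5268 = 0.074, so power = 52.9%. Exact enumeration of the Pearson test gives 53.9%.
- *GV-EA vs rehabilitation:* d = 0.30, p̄ = 0.75. √(2 × 0.75 × 0.25) = 0.6124; √(0.09 + 0.24) = 0.5745. (2.1840 − 1.2002)/0.5745 = 1.71, so power = 95.7%.

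**4. Size needed for 90% power, GV-EA vs conventional EA.** n = (1.960 × 0.5374 + 1.2816 × 0.5268)²/0.15² = 1.7283²/0.0225 = 132.8, so 133 evaluable per arm.

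**5. Sensitivity of the GV-EA vs conventional EA power.**

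| Setting | Power |
|---|---|
| 53 per arm, two-sided 0.05 | 52.9% |
| 59 per arm (no dropout), two-sided 0.05 | 57.5% |
| 53 per arm, alpha 0.025 (two comparisons, Bonferroni) | 41.6% |
| 53 per arm, one-sided 0.05 | 65.4% |

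No setting comes near 90%.

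**6. How often the two tests part company.** In simulations at the assumed rates with 53 per arm, the three-group test is significant while GV-EA vs conventional EA is not in about 40% of trials.

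**The case against.** Nothing in the sponsor's arithmetic is wrong: 53, 59 and 177 all reproduce. Powering a three-group test is legitimate, and GV-EA versus rehabilitation is well covered. That stands. The fault is that the powered comparison is not named, so the stated type 2 error appears to apply where it does not. The three-group test is itself inferred from an exact numerical match.

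A reader might infer that the plan contains no GV-EA versus control comparison. The documents do not support that. Section 2.1 announces both comparisons, and post hoc pairwise tests are a detail an article commonly leaves to the full protocol or analysis plan, neither of which is shown.

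A reader might also infer that the trial would claim GV-EA superiority whenever the omnibus test is significant, even with GV-EA equal to conventional EA. The article nowhere says the omnibus result will be read that way, and any figure for how often this would happen on RMS or the MAS needs effect sizes the document does not give.

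The most substantial objection is that the calculated powers belong to an effectiveness rate that is not a listed primary or secondary outcome and has no named test in section 4.4. This is correct, and it limits the point. The figures test section 2.7 against its own assumptions. They are not the power for RMS or the MAS, which cannot be derived: no mean difference is given, and the SD of 10 is tied to no outcome. This does not rescue the type 2 error statement, which rests on those same rates.

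Finally, no particular testing order is required. With three arms, an omnibus test followed by pairwise tests at 0.05 is already a closed procedure. Simulated power for GV-EA versus conventional EA was about 53% that way and about 53% by a fixed sequence starting with rehabilitation.

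**Conclusion.** The point holds in this form: on section 2.7's own assumed rates, the stated type 2 error of 0.1 does not apply to GV-EA versus conventional EA, a comparison that sections 2.1 and 2.6.3 make a purpose of the trial. Its type 2 error there is about 0.47 (1 − 0.529). The shortfall is confined to that comparison.

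This rests on the rates of 90%, 75% and 60%, a two-sided unadjusted 0.05 test and 53 evaluable per arm. It also rests on reading the undeclared calculation as a three-group chi-square test, although the pairwise powers hold whichever test was used to reach 53. It is a mismatch between declared power and stated purpose, not an arithmetic error, and it does not show that the trial must be enlarged.

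**What to change.** **Section 2.7.** State that 53 evaluable patients per group give 90% power for the three-group test of the assumed effectiveness rates only. Add the pairwise powers at two-sided 0.05: about 96% for GV-EA versus rehabilitation and about 53% for GV-EA versus conventional EA. Note that all three figures refer to the effectiveness rate and not to the listed primary outcomes, RMS and the MAS.

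**Section 4.4.** State that conclusions about GV-EA against each control rest on the pairwise contrasts, reported with 95% confidence intervals for each primary outcome, and not on the omnibus P value alone. The multiplicity procedure is the sponsor's choice; an omnibus test followed by pairwise tests as a closed procedure, or a fixed sequence, would both serve.

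**Cost.** Wording in two sections and no more patients. The price is a visibly less favourable power for GV-EA versus conventional EA, so a non-significant result there should be reported as inconclusive unless its confidence interval says otherwise.

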### 2.8. Outcome Assessments

The observation indexes of result measurement include three parts: baseline, safety indicators (general physical examination, routine blood tests, routine urine tests, routine stool tests, electrocardiograms, and liver and kidney function tests), and clinical efficacy observation indexes. All evaluations will be performed before and after treatment.

### 2.9. Primary Outcomes

The main result is surface electromyography (sEMG) measurement and the Modified Ashworth Scale (MAS).

### 2.10. Surface Electromyography (sEMG) Measurement

The sEMG, also known as dynamic electromyography, is a widely used technology in rehabilitation research and provides quantifiable information on the myoelectric output of a muscle [20]. It is a noninvasive inspection method for recording bioelectric signals during muscle activity through surface electrodes and is an essential test tool for studying the functional status of the neuromuscular system. At the same time, it provides a scientific basis for clinical treatment. Commonly used evaluation indicators for sEMG include frequency and time-domain indicators, among which time-domain indicators mainly include the root mean square (RMS). Among them, the RMS value reflects the change of the amplitude of the sEMG signal voltage in the time dimension and variation of relevant muscle strength [21]. Its change mainly reflects the number of motor units activated during muscle activity, the type of motor units participating in the activity, and the degree of synchronization. The sEMG can also distinguish between spasticity and contracture. When the joint resistance measured by passive stretching increases and the antagonistic myoelectric signal is not significantly different from the resting state, it is a contracture, and the electromyographic signal is significantly increased, which is spasticity.

Before and after the treatment, the sEMG signal system (BioNeuro Infiniti, Thought Technology Ltd., Canada) was used to collect the electromyographic signal values of the quadriceps, hamstrings, calf triceps, and tibialis anterior muscles of the hemiplegic lower limbs. With the patient in the sitting position, a 75% alcohol cotton swab will be used to clean the skin on the measured muscle surface to remove oil on the skin surface, reduce electrical resistance, and increase the electrical conductivity between the surface electrode and the skin. After cleaning, according to the anatomical position of the muscle and the direction of the muscle fiber, the disposable surface electrode sheets are, respectively, pasted on the muscle belly of the measured muscle. Select the program measurement mode, passively stretch the tested muscles, passively stretch 3 times, relax 3 times, 5 s each time, take RMS value as the detection index, and calculate cocontraction ratios (CCR); the specific calculation formula is

CCR = antagonist muscle RMS/(active muscle RMS + antagonist muscle RMS)

## 3. The Modified Ashworth Scale (MAS) [22]

The MAS is the most widely used spasticity assessment and has the advantages of simplicity, time savings, and convenient operation, which includes 6 levels. To facilitate data recording and analysis and statistical analysis, grades 0, I, I+, II, III, and IV are converted into 0, 1, 2, 3, 4, and 5 points, respectively. The higher the MAS score is, the more serious the spasticity is considered as shown in Table 3.

### 3.1. Secondary Outcomes

The Fugl–Meyer Assessment for Lower Extremity (FMA-LE) and the Modified Barthel Index score (MBI) were the secondary observation outcome indicators.

## 4. The Fugl–Meyer Assessment for Lower Extremity (FMA-LE)

The FMA-LE is a widely recognized and valid clinical measure of poststroke motor impairment severity assessment. The lower extremity has a maximum score of 34 points divided into motor, balance, sensory, range of motion, and joint pain and a higher score indicates better lower limb movement function [23, 24]. The FMA-LE is the most common scale for evaluating lower limb motor function after stroke.

### 4.1. The Modified Barthel Index Score (MBI)

The MBI is mainly used to assess the patient's daily living ability, including control urination, eating, grooming, toileting, transfer, walking, dressing, bathing, and going up and down stairs. The total score is 100 points. A higher score indicates the worst daily living ability. The MBI classification can be divided into without dependence (100 points), mild dependence (61∼99 points), moderate dependence (41∼60 points), severe dependence (1∼40 points), and completely dependent (0 points) [25].

### 4.2. Safety Evaluation and Adverse Events

Any adverse events and how they are dealt with will be recorded throughout the treatment process. Adverse events related to acupuncture treatment included severe pain, fainting, bleeding, or other any discomfort. During the intervention period, the researchers will pay close attention to the patient's condition. If any discomfort occurs to the patient, the intervention will be stopped immediately and the patient's condition will be dealt with accordingly. Any medical occurrence detailed information will be reported in detail in case report forms (CRFs). The primary researchers will review all adverse events periodically, and the Ethics Committee will have access to the interim results.

### 4.3. Data Collection and Management

The data of all patients will be recorded on the CRFs, which include observation time points, outcome measures, adverse events, safety evaluations. Two independent researchers will input the data into the Excel spreadsheet, and each patient's personal privacy information will be protected. Data will be safely kept by the data researchers of our team and monitored by the Ethics Committee of the First Affiliated Hospital of the Henan University of Chinese Medicine each year as shown in Table 1.

### 4.4. Statistical Analysis

Statistical analysis will be performed using SPSS 25.0 software for statistical analysis. To measure baseline, a chi-square test or analysis of variance (ANOVA) is used to compare demographic data and other basic data at baseline. Continuous variables are expressed in terms of mean ± standard deviation when following a normal distribution. If not, the data will be shown by medians and interquartile ranges. Frequencies and percentages will be used to count the data. The paired *t*-test will be used to compare the differences between the groups before and after treatment, including the RMS value, FMA-LE, and MBI score. The comparison among the three groups before and after treatment will be analyzed by variance (ANOVA). For the MAS, the Kruskal–Wallis test will be used. The test level is set to 0.05, and *P* < 0.05 means the difference is statistically significant.

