### 2.5. Inclusion and Exclusion Criteria

#### 2.5.1. Inclusion Criteria

Participants meeting the following criteria will be included:Patients who meet the diagnostic criteria of stroke by computed tomography (CT) or magnetic resonance imaging (MRI) (including ischemic and hemorrhagic stroke).Patients with the Modified Ashworth Scale of grade I and above, grade III and below.First onset, subacute stage of stroke (the onset time is 3 weeks to 6 months).Males or females with an age range between 20 and 70 years.Patients with stable vital signs, no cognitive impairment, and cooperate with treatment.Patients who voluntarily agree and sign the informed consent form.

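### The paired t-test is assigned to a between-group question it cannot answer, and the group comparisons that follow leave out baseline adjustment, at a cost mainly in precision

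*Protocol article*

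**What the plan says.** All of the analysis text is in the protocol article, section 4.4 (Statistical Analysis).

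- **Paired t-test.** It "will be used to compare the differences between the groups before and after treatment, including the RMS value, FMA-LE, and MBI score".
- **Three-group test, continuous outcomes.** "The comparison among the three groups before and after treatment will be analyzed by variance (ANOVA"). No covariate is named, and the text does not say whether the ANOVA is run at each time point or on the change.
- **Three-group test, ordinal outcome.** "For the MAS, the Kruskal–Wallis test will be used". Again no covariate is named.
- **Role of baseline data.** A chi-square test or ANOVA "is used to compare demographic data and other basic data at baseline". This is the only use of baseline data that is spelled out.
- **Decision rule.** "The test level is set to 0.05". The rule is attached to no particular test.

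Table 1 schedules RMS, MAS, FMA and MBI at week 0 and again at week 4, so every outcome has a baseline value. Section 2.1 gives the aim as the efficacy of GV-EA relative to conventional EA and to rehabilitation treatment.

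**The concern.** A paired t-test works on two measurements in the same patients. It asks whether the mean change in one group is zero and cannot say whether one randomised arm changed more than another. Section 4.4 nevertheless gives it the between-group question for three of the four outcomes.

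The setting makes within-group change a poor guide to the effect of GV-EA. Every arm receives routine drugs and rehabilitation (section 2.6), and patients are enrolled in the "subacute stage of stroke (the onset time is 3 weeks to 6 months") window. Some change in every arm is therefore plausible whatever GV-EA does. Only a contrast between arms answers the aim in section 2.1.

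The second issue is efficiency. The baseline value of an outcome usually predicts its final value. A group comparison that leaves it out as a covariate has wider intervals than the collected data allow. Leaving open whether the ANOVA uses the week-4 value or the change also means that the primary RMS result has two possible forms.

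**Working it through.** **1. The plan's own figure.** Section 2.7 assumes that "the effectiveness rate of conventional EA and rehabilitation treatment is about 75% and 60"% respectively, with 90% for GV-EA, and states: "Type 1 error is assumed at 0.05, type 2 error is assumed at 0.1, and a standard deviation is 10". The method is not named, but an overall 3 × 2 chi-square test reproduces the result:

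- mean rate = (0.90 + 0.75 + 0.60)/3 = 0.75
- w² = [(0.15² + 0² + 0.15²)/3] / (0.75 × 0.25) = 0.015/0.1875 = 0.08, so w = 0.283
- at 53 per group, N = 159 and the noncentrality is 159 × 0.08 = 12.72. With 2 degrees of freedom and alpha 0.05, power is 0.902
- 53/0.9 = 58.9, rounded up to 59 per group, and 3 × 59 = 177

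The stated 53, 59 and 177 are confirmed, and the SD of 10 plays no part. This calculation concerns a response rate, so it does not show which analysis of RMS or MAS is meant to be decisive. Nothing below changes the sample size. I use n = 53 per arm.

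**2. Precision given up without a baseline covariate.** Let r be the correlation between the baseline and week-4 values, with equal variance at both times. The document gives no r, so the values are assumptions. In units of the week-4 variance:

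- post-only ANOVA: 1
- change-score ANOVA: 2(1 − r)
- ANCOVA: 1 − r²
- ANCOVA relative to change score: (1 − r²)/[2(1 − r)] = (1 + r)/2

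| r (assumed) | ANCOVA vs post-only | ANCOVA vs change | 53 per arm with ANCOVA matches post-only n of | matches change-score n of |
|---|---|---|---|---|
| 0.3 | 0.91 | 0.65 | 58 | 82 |
| 0.5 | 0.75 | 0.75 | 71 | 71 |
| 0.7 | 0.51 | 0.85 | 104 | 62 |
| 0.8 | 0.36 | 0.90 | 147 | 59 |

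The last two columns are 53 divided by the variance ratio. Over this range the variance reduction is 9% to 64% against post-only, and 35% down to 10% against change scores. These formulas are for continuous outcomes. They do not apply to the MAS, which is ordinal and restricted at entry to grades I to III.

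**3. What would follow if separate paired tests were read as group evidence.** Suppose that all arms have the same true change, with d the mean change divided by the SD of the change. The document gives no d, so this is also assumed. Let p be the power of a two-sided paired t-test at 0.05 with n = 53 (52 degrees of freedom, noncentrality d√53).

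| d (assumed) | p | Two arms disagree, 2p(1 − p) | GV-EA significant, one given control not, p(1 − p) | GV-EA significant, at least one control not, p(1 − p²) |
|---|---|---|---|---|
| 0.2 | 0.298 | 42% | 21% | 27% |
| 0.3 | 0.573 | 49% | 24% | 39% |
| 0.4 | 0.815 | 30% | 15% | 27% |
| 0.5 | 0.947 | 10% | 5% | 10% |

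The third column counts disagreement in both directions, including patterns that go against GV-EA. The last two columns count only patterns that could be taken to favour it.

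**The case against.** The best defence is that the paragraph should be read as a whole. Directly after the paired t-test, it assigns ANOVA and Kruskal–Wallis to the comparison among the three groups. The paired sentence then most plausibly means change within each group, with the word between as a slip. This largely stands. Proper group tests are specified, and a reader who infers that efficacy will be claimed because GV-EA is significant and a control is not goes beyond the text. The protocol states no such rule. The percentages in step 3 of the working are therefore conditional and are not a false-claim rate for this trial. They are highest at d of 0.2 to 0.3. If all arms improve substantially, as the setting suggests they may, d is larger and disagreement becomes rarer.

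A second defence is that baseline adjustment is an efficiency choice, often left to an analysis plan that is not shown here. This stands in part. With 1:1:1 randomisation the unadjusted tests are valid. A reader might infer that the results would be biased, but the loss is one of precision, and chance imbalance is already covered by the type 1 error. It would also be too strong to say that no planned comparison can use the baseline value, because an ANOVA on change scores does so.

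Two things survive. The mislabelled test is stated in the text, so it is not something merely left to another document. The text also fixes ANOVA without saying on what quantity, and does not say which test decides.

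**Conclusion.** The point holds in limited form and should be fixed, but it does not invalidate the trial. Section 4.4 gives a within-group test a between-group job for RMS, FMA-LE and MBI. The valid group tests beside it have no baseline covariate, an undefined ANOVA quantity and no stated priority.

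The main cost is precision. At r = 0.5 and 0.7, ANCOVA would have 25% and 49% less residual variance than a post-only comparison, and 25% and 15% less than a change-score comparison. These figures rest on the assumed r and on equal variances at the two times. No gain has been quantified for the MAS.

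The risk of misreading paired tests is secondary. Two arms with the same true change would disagree on significance in about 42%, 49%, 30% and 10% of trials at assumed d of 0.2, 0.3, 0.4 and 0.5, counting both directions. That risk arises only if someone draws an inference that the plan does not state.

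**What to change.** In section 4.4, or in the analysis plan before the data are examined by group:

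1. Relabel the paired t-test as a descriptive summary of change within each group, and state that no efficacy conclusion will be drawn from it.
2. For RMS, FMA-LE and MBI, name as the decisive comparison an ANCOVA of the week-4 value on treatment group, with the baseline value of the same outcome as covariate. This also settles whether post-treatment or change scores are analysed.
3. For the MAS, preferably use an ordinal model of the week-4 grade with baseline MAS as covariate. If Kruskal–Wallis is kept, it remains valid, but the quantity compared should be stated.
4. Report GV-EA against conventional EA and GV-EA against rehabilitation treatment, each as an estimated difference (for the MAS, the model's effect measure) with a 95% confidence interval.

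The cost is wording. Table 1 already collects every value needed, SPSS fits these models, and the stated sample size of 59 per group does not change.

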## Abstract

*Background*. Lower limb spasticity is a common complication after stroke, which seriously affects the quality of life and rehabilitation of patients. There are different treatment methods for poststroke spasticity. It has been found in clinical practice that governor vessel electroacupuncture (GV-EA) can effectively relieve poststroke upper extremity spasticity, but the efficacy of treatment of lower extremity spasticity needs to be further verified. This study aims to design a randomized controlled trial to evaluate the efficacy of GV-EA in the treatment of poststroke lower limb spasticity. *Methods/Design*. This is a randomized, controlled trial. Patients (*N* = 177) will be randomized to receive routine therapeutic drug and rehabilitation treatment plus GV-EA (experimental group) or routine therapeutic drug and rehabilitation treatment plus EA (control group 1) or routine therapeutic drug and rehabilitation treatment (control group 2). All patients will receive 20 sessions of treatment for 4 weeks. The primary outcomes are the RMS value and the Modified Ashworth Scale. Secondary outcomes include the Fugl–Meyer Assessment for Lower Extremity (FMA-LE) and the Modified Barthel Index score. All outcome measures will be evaluated at the beginning and after the intervention (4 weeks). *Discussion*. This trial will observe the clinical effect of GV-EA on lower extremity spasticity after stroke, especially its influence on surface electromyography characteristics, and provide high-quality experimental evidence for the clinical application of GV-EA based on surface electromyography in the treatment of poststroke lower limb spasticity. *Trial Registration*. China Clinical Trials Registry No. ChiCTR1900027969. Registered on 7 December 2019.

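### Two unranked primary outcomes, one of them spread over four muscles, are each tested at 0.05 with no order, adjustment or success rule

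*Protocol article*

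**What the plan says.** The Abstract states: "The primary outcomes are the RMS value and the Modified Ashworth Scale". Section 2.9 names the same pair but describes the first more broadly, as sEMG measurement. Neither place ranks the two.

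Section 2.10 collects "the electromyographic signal values of the quadriceps, hamstrings, calf triceps, and tibialis anterior muscles of the hemiplegic lower limbs". The instruction for each muscle is "passively stretch 3 times, relax 3 times, 5 s each time, take RMS value as the detection index", and co-contraction ratios (CCR) are derived as well. No muscle is singled out as primary. Section 3 describes the MAS grades and their conversion to points but names no joint or muscle group.

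Section 4.4 assigns ANOVA over the three groups to the continuous outcomes and Kruskal–Wallis to MAS, then sets one rule for all of them: "The test level is set to 0.05", with any P value below that counted as significant. It gives no testing order, no adjustment, and no statement of how many primary results must be significant.

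**The concern.** A per-test level of 0.05 gives a 5% error rate for the primary claim only if one test decides it, or if every named test must succeed. Here at least two tests carry primary status. Because the RMS outcome is four muscles with none chosen, the count is naturally five. Under the rule as written, a report could rest its efficacy claim on MAS alone or on any single muscle, and each would meet the stated criterion. The reader could not then tell what error rate stands behind the claim.

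**Working it through.** **Inputs from the protocol article**
- Two primary outcomes, RMS and MAS (Abstract, section 2.9).
- Four muscles (section 2.10).
- Level 0.05 for every test (section 4.4).
- Sample size: effectiveness rates 90%, 75% and 60%, type 1 error 0.05, type 2 error 0.1, 53 per group, 10% dropout, 59 per group and 177 in total (section 2.7).

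**Assumption.** The correlation between the primary tests is not given, so a range is shown.

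**1. The plan's own figure.** The 53 per group reproduces as a single three-group chi-square test (2 df) at the full 0.05.
- Mean rate = (0.90 + 0.75 + 0.60)/3 = 0.75.
- Effect size w² = [(0.15² + 0 + 0.15²)/3] / (0.75 × 0.25) = 0.015/0.1875 = 0.08.
- Noncentrality at 159 patients = 159 × 0.08 = 12.72. With critical value 5.99, power is 90%.
- Dropout: 53/0.9 = 58.9, so 59 per group, and 3 × 59 = 177.

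The calculation therefore spends the whole 0.05 on one test, of an effectiveness rate that is neither RMS nor MAS. Nothing is set aside for several primary tests.

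**2. Independent tests.** The chance of at least one P < 0.05 when nothing works is 1 − 0.95^m.
- m = 2 (one RMS variable, one MAS): 1 − 0.9025 = 9.8%.
- m = 5 (four muscles, MAS): 1 − 0.7738 = 22.6%.
- m = 9 (four muscles in two states, MAS): 1 − 0.6302 = 37.0%.

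**3. Correlated tests.** Simulation of 20,000 null trials, 59 per arm, one 2-df ANOVA F test per outcome at 0.05 (MAS approximated by the same test), equal correlation between outcomes:

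| Tests | Correlation 0.5 | Correlation 0.7 |
|---|---|---|
| 2 | 9.2% | 8.9% |
| 5 | 18.7% | 15.3% |
| 9 | 28.2% | 20.9% |

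A separate simulation with correlated normal statistics (400,000 draws) gives nearly the same: 9.1% and 8.4% for two tests, 18.2% and 14.9% for five, 26.8% and 20.3% for nine.

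**4. The opposite reading.** If success required MAS and at least one RMS result, the error when nothing works would be about 1–3% over the correlations tried. That protects only against the case in which neither outcome responds. If MAS truly improved and no muscle did, an at-least-one-muscle rule would still declare RMS positive in up to 1 − 0.95⁴ = 18.5% of trials (independent tests).

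**5. Price of a split level.** In the section 2.7 calculation at 0.025, the critical value is 7.38 and power at 53 per group is about 84%. Keeping 90% needs 185 patients, that is 62 per group, or 62/0.9 = 68.9, so 69 per group after dropout.

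Pairwise group comparisons, the within-group paired t-tests and the interim look at 89 cases are not in these figures.

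**The case against.** The strongest reply is that a journal article condenses a fuller protocol, and that multiplicity adjustment, the averaging of repeats and the MAS site are commonly settled in an analysis plan that is not shown. That stands for the averaging of the three stretches and for the MAS site: their absence alone would be no finding. It does not remove the point, because the article does state a decision rule, a flat 0.05 for every test, and applies it to two primaries of which one is four variables.

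Four stronger readings are tempting and should not be adopted.

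- **That the plan lets any one significant result win.** It states no success rule at all. The inflated figures are conditional on that reading.
- **That the false-positive chance is one in five.** Neither the number of tests nor their correlation is in the document. That figure fits five tests at a correlation of about 0.4, or nine at about 0.7. The nine-test count also presumes that RMS at relaxation is analysed separately, whereas relaxation may be only the pause between stretches.
- **That the favourable direction of RMS could be chosen after seeing the data.** The Introduction treats a fall in RMS as improvement in the earlier upper-limb study, and section 2.10 ties a raised signal under passive stretch to spasticity. Lower is therefore better. The remarks on muscle strength and motor units are general background.
- **That CCR adds to the primary error rate.** The Abstract names the RMS value, and Table 1 lists RMS, MAS, FMA and MBI but not CCR.

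**Conclusion.** The concern holds in limited form. Two primary outcomes are unranked, the RMS outcome is not reduced to one variable, and the stated level is per test. If any one significant primary result supports efficacy, the false-positive chance is about 8–10% for two tests and about 15–23% for five, for assumed equal correlations from 0.7 to 0. It is about 20–37% for nine tests, should relaxation values also be tested. If both outcomes had to succeed there would be no inflation when nothing works. The defect is that the document leaves the error rate of its main claim to an unstated rule, while the only rule it does state permits the inflated reading.

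**What to change.** In sections 2.9, 2.10 and 4.4, before any analysis:

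1. Name one primary RMS variable: one muscle chosen by the sponsor, during passive stretch, as the mean of the three stretches, with lower values favourable.
2. Name one MAS site.
3. State the rule for these two. Either test them with Holm or in a fixed order at an overall 0.05, or require both to be significant at 0.05 each.
4. Make the other muscles, any relaxation values and CCR secondary.

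No new measurements are needed. The cost depends on the rule:

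- **Holm:** the smaller P value must pass 0.025. On the section 2.7 calculation that means about 84% power at 53 per group instead of 90%, or 62 per group to restore 90%. This is indicative only, since that calculation concerns neither primary outcome.
- **Fixed order:** the first test keeps 0.05, but the second cannot be claimed if the first fails.
- **Both required:** each test keeps 0.05, but joint power falls. Two independent tests with 90% power each give 0.9 × 0.9 = 81%, and positive correlation gives more.
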